### Design

The effectiveness of the intervention is being tested through a cluster randomised controlled trial. Because the intervention is targeted at communities, the unit of allocation is the VDC cluster. We randomly allocated the 43 VDCs in the district to receive the intervention (n = 21) or serve as control areas (n = 22). We have already worked in 30 VDCs in Makwanpur district to evaluate the effectiveness of women's group interventions, and we felt it was important to stratify sampling on the basis of previous exposure of clusters to programme activities. The success of these activities had led to measurable differences between VDCs. We stratified clusters into four groups. Group 1 included control clusters from 2002-2005, and intervention clusters from 2005 to 2008. Group 2 included intervention clusters from 2001-2008. In group 3 we monitored birth outcomes from 2005-2008. In group 4, we had not previously conducted any intervention or monitoring activities. We randomly allocated equal numbers of clusters from each group to intervention and control clusters using the methods detailed below. Although the cluster number is large, and it is possible that unstratified allocation would lead to a balanced design, we preferred a stratified design because of its intelligibility to residents of the district (see Figure 2).

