### Sample size

The study will include all pregnancies in all 43 VDCS. We estimate that each VDC will yield about 100 births per year and that the proportion of birth attendance by trained health workers is currently 20%. We estimated sample size using the equations of Hayes and Bennett [57], assuming two treatment groups and unmatched clusters of approximately equal size. We set a value of *k *- the between-cluster coefficient of variation - equal in intervention and control groups, and added 2 to the estimated cluster number to account for loss of degrees of freedom as a result of stratification. All estimates are based on a two-tailed 5% significance level. The value of *k *is likely to be 0.3 on the basis of estimates of neonatal mortality rate from the Makwanpur study. However, we have estimated sample size with a range of *k *from 0.25 to 0.35.

For two years of intervention (200 births per cluster), if *k *= 0.35, 42 clusters would detect an increase in trained attendance from 20% to 30% at 90% power, and from 20% to 28% at 80% power. If *k *= 0.30, 42 clusters would detect an increase in trained attendance from 20% to 28% at 90% power, and from 20% to 27% at 80% power. If *k *= 0.25, 42 clusters would detect an increase in trained attendance from 20% to 27% at 90% power, and from 20% to 26% at 80% power. Overall, a conservative level of powers, births and values of *k *suggests that the sample size will be able to detect an increase in birth attendance by trained health workers of around 10% over two years.

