#### Analysis strategies

Data will be checked for consistency and completeness in both the RDBMS and after export to Stata. An analysis plan will be developed in accordance with the CONSORT reporting guidelines [67]. We will present a trial profile and a comparison of key variables between intervention and control arms at baseline. Details of the number of clusters and individuals included in the analysis will be provided, and the analysis will be intention-to-treat. We will compare the primary outcome in intervention and control arms, using data for two years of intervention. We will conduct the analysis at the level of the individual, and the procedure of choice will be random effects logistic regression models grouped on cluster. If quadrature checks suggest that this is inappropriate, we will use generalised estimating equations. Analyses will be adjusted for socioeconomic status and religion. The findings will be augmented by ancillary analyses, which may include dose-response, interrupted time series and process evaluations.

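### The stated primary model leaves out the four allocation strata, which makes the test conservative if the strata predict trained attendance; add them, with small-sample inference

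*Protocol article*

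**What the plan says.** **Design.** "We stratified clusters into four groups", defined by previous exposure to programme activities, because "The success of these activities had led to measurable differences between VDCs". The section gives a second reason as well: "we preferred a stratified design because of its intelligibility to residents of the district". On the allocation itself: "We randomly allocated equal numbers of clusters from each group to intervention and control clusters". The totals are 21 intervention and 22 control clusters.

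**Sample size.** The calculation uses the Hayes and Bennett equations for unmatched clusters and "added 2 to the estimated cluster number to account for loss of degrees of freedom as a result of stratification".

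**Analysis strategies.** At the level of the individual, "the procedure of choice will be random effects logistic regression models grouped on cluster", with generalised estimating equations if quadrature checks fail. On covariates: "Analyses will be adjusted for socioeconomic status and religion". The strata are not mentioned. The same section announces a later document: "An analysis plan will be developed in accordance with the CONSORT reporting guidelines".

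**The concern.** The three sections do not fit together. The design restricts allocation by stratum, the sample size pays for fitting the strata, and the model that is named does not fit them. An analysis loses degrees of freedom to stratification only if it contains stratum terms.

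Stratified allocation keeps the arms nearly balanced on the strata, so differences between strata contribute almost nothing to the true sampling error of the treatment effect. A model without stratum terms leaves those differences in the cluster random effect and counts them as error. The reported standard error then exceeds the true one.

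The strata plausibly matter for this outcome. The Background section reports that the earlier trial in the same district found significant positive differences in institutional delivery and trained attendance, and the strata record which clusters had that programme and when. What is at stake is power and interval width.

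**Working it through.** **1. The plan's own figures.** Inputs from Sample size: p0 = 0.20, m = 200 births per cluster, 21 clusters per arm, two-sided 5%, k from 0.25 to 0.35. Per arm,

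c = a + (z_0.975 + z_power)² × [p0(1−p0)/m + p1(1−p1)/m + k²(p0² + p1²)] / (p1 − p0)².

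For k = 0.30, p1 = 0.27 and 80% power: 7.849 × (0.00080 + 0.00099 + 0.01016) / 0.0049 = 19.14, plus a. Solving for p1 at 21 clusters per arm gives:

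| k, power | Stated p1 | a = 2 per arm | a = 1 per arm |
|---|---|---|---|
| 0.35, 90% | 30% | 29.9% | 29.6% |
| 0.35, 80% | 28% | 28.3% | 28.05% |
| 0.30, 90% | 28% | 28.4% | 28.15% |
| 0.30, 80% | 27% | 27.05% | 26.85% |
| 0.25, 90% | 27% | 27.0% | 26.8% |
| 0.25, 80% | 26% | 25.95% | 25.75% |

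The stated figures reproduce to the whole percent whether the 2 clusters are added per arm or in total.

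**2. Hand check of the mechanism.** Take k = 0.30 as the total between-cluster variation, strata included.
- Between-cluster variance on the logit scale is about (k/(1−p0))² = (0.30/0.80)² = 0.1406.
- Sampling variance of a cluster's log odds is about 1/(200 × 0.20 × 0.80) = 0.0313.
- With stratum share s, the ratio of true to reported standard error is √{[(1−s) × 0.1406 + 0.0313] / 0.1719}.
- s = 10%: √(0.1578/0.1719) = 0.96.
- s = 25%: √(0.1367/0.1719) = 0.89.
- s = 50%: √(0.1016/0.1719) = 0.77.

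The reported standard error is therefore about 4%, 12% and 30% too large (1/0.96, 1/0.89, 1/0.77).

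**3. Simulation, cluster-level t-test.** 43 clusters of 200 births, k = 0.30, analysed on cluster log odds with 41 degrees of freedom without strata (43 − 2) and 38 with them (43 − 5). There were 20,000 null runs and 8,000 runs under 20% to 27%. Stratum sizes 12/12/6/13 (intervention 6/6/3/6) are an assumption; they fit the six balls drawn in the first stratum, the 30 areas with earlier work and the total of 21.

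| Stratum share (assumed) | Null rejection, without v with strata | Power, without v with strata |
|---|---|---|
| 0% | 4.6% v 4.7% | 76.2% v 76.4% |
| 10% | 4.2% v 5.1% | 77.5% v 79.1% |
| 25% | 2.9% v 4.9% | 79.2% v 84.1% |
| 50% | 1.1% v 4.6% | 85.2% v 93.6% |

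The empirical spread of the estimate is the same with and without strata (0.127 v 0.127 at 25%, 0.107 v 0.107 at 50%), so the loss lies in the reported error. Under the null the mean log odds ratio without strata is at most 0.006, so bias is negligible.

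**4. Simulation, the stated mixed model.** At k = 0.30, stratum terms cut the reported standard error by about 16% (30% share) and 26% (50% share) and raised power for 20% to 27% by about 4 to 8 points. At k = 0.35, maximum likelihood with a Wald z test (2,500 null runs per share) gave null rejection, without v with strata, of:
- 0% share: 6.0% v 6.9%
- 10%: 5.7% v 7.8%
- 30%: 3.1% v 7.5%
- 50%: 1.4% v 8.4%

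Part of the apparent gain in that model is thus an understated standard error. Stratum terms alone do not give a 5% test.

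**The case against.** **The omission may be condensation.** The article does not say that socioeconomic status and religion are the only covariates, and it promises an analysis plan. The allowance for stratification suggests that a stratified analysis was intended. This stands as far as intent goes: a reader might infer a decision to exclude the strata, and the text does not support that. The point survives because the article does list its model and adjustment set, and the list does not match its design and sample-size sections.

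**The error is in the safe direction.** This stands. A reader might infer from a miscalibrated test that a positive result would be unreliable. Leaving out the strata does the opposite: it lowers the rejection rate.

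**The stratum share is unknown.** This also stands. The article names neither the outcome nor the size of the measurable differences. Groups 1 and 2 both had the intervention in 2005-2008, most women in the earlier study still gave birth at home without a trained worker, and socioeconomic status and religion may absorb part of the stratum differences. At a 10% share the effect is small.

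**Power may be adequate anyway.** A mixed-model simulation at k = 0.35 for 20% to 28% gave 90% and 92% power without strata (30% and 50% shares). That used a Wald z test and a normal logit random effect. The cluster-level t-test, with k applied to the proportion itself, gave 74% and 80% at 25% and 50% shares for the same effect, against 79% and 90% with strata. The absolute level depends on the simulation model, so no claim is made that the trial misses its target.

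**The 21 v 22 split.** A reader might see an imbalance that needs correcting. One cluster is trivial, as the mean estimates show.

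**Conclusion.** The point holds as a should-fix. As written, the primary model ignores the strata used for randomisation, against the article's own design rationale and its own allowance in the sample size. If the strata predict trained attendance, the test is conservative and the interval too wide.

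For 20% to 27% at k = 0.30 the power forgone is nil at a 0% share, about 1.6 points at 10% (77.5% v 79.1%), and roughly 4 to 9 points at 25% to 50%. This rests on assumed stratum sizes, an undocumented stratum share, and k read as total between-cluster variation. The direction does not depend on the assumed sizes.

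The documents do not support a stronger reading. The estimate is essentially unbiased, the omission does not inflate false positives, and the share could be small. Nor would adding stratum terms be enough by itself, because with a Wald z test it would exchange a conservative test for a mildly liberal one.

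**What to change.** In Analysis strategies, state that the random-effects model and the GEE fallback both include the four allocation strata as fixed effects (three indicator terms), in addition to socioeconomic status and religion.

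State in the same place that inference will be based on the number of clusters. Options are a stratified cluster-level t analysis, or a degrees-of-freedom and variance correction for the mixed model or GEE. The two parts belong together.

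The cost is a sentence or two and three degrees of freedom (41 to 38 at cluster level). The sample size already makes some allowance for stratification, although it is expressed as 2 clusters rather than as 3 degrees of freedom. No new data are needed, and at a zero stratum share nothing material is lost. The change should be fixed before outcome data are compared by arm, so that it cannot look data-driven.

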### Ethical issues

The study was approved by the Nepal Health Research Council on 12^th ^February 2009, and the University College London Ethics Committee on 13^th ^September 2010.

Before allocation, we conducted community meetings in each VDC cluster, usually in the health facility building, school or community hall. We invited the chairperson of the HMC, representatives of local and international non-governmental organisations, community based organisations, teachers, FCHVs, political leaders, health personnel, political representatives, and social leaders. We aimed to have at least 20 people present at each community meeting and between 17 and 49 people attended. We presented our previous research and current research plan, our objectives and the utility of the research using graphs and pictures for ease of understanding. There followed an open discussion, question and answer session, and written consent to conduct the study was taken at the cluster allocation meeting. In addition, interviewers approach respondents in their homes, provide information and then take verbal consent before conducting interviews. After trying to obtain written consent with some respondents who were literate, we decided that, for consistency, it would be better to take informed verbal consent in this largely illiterate population. Participation in the HMC or women's group intervention is voluntary and based on personal interest. Participants are free to opt in or out as they wish.

#### Benefits to control areas

During previous research in the district, we have given Essential Newborn Care training to all health personnel and FCHVs, and have provided basic equipment for newborn care in health facilities. In the current trial, we will train all health workers in the district in Obstetric First Aid and re-supply essential newborn care equipment. This ensures a minimum level of care in the study area.

#### Sustainability and scalability

We are working with the government cadre of the FCHV to implement the women's group intervention, which increases the sustainability of our approach. We found that 77% (n = 183) of groups mobilised in previous interventions were continuing to meet 12 months after MIRA stopped supporting them. Half of these groups were being facilitated by the FCHV and a group member ran the other half. 60% of groups were confident that they would continue meeting for the next two years[68]. This suggests community ownership and integration, and increased potential for the intervention and its effects to endure beyond the trial.

We have trained district level health personnel in an Appreciative Planning and Action approach and they have facilitated sessions at every workshop with HMCs. Political representatives, health personnel, and community members participated in HMC strengthening workshops, with district level employees, creating linkages and strengthening communication between local and district level personnel. Through strengthening existing local structures of FCHV-led women's groups and HMCs, we seek to enable sustained linkages between health facilities and communities. We hope to enable communities to maintain improved services by building local capacity and commitment to change.

### Public engagement

We will promote public engagement in our research locally, nationally and internationally.

Locally, we have been engaged in dialogue with community representatives, political bodies, community-based organisations (CBOs) and NGOs since cluster allocation. Intervention areas will have formal community meetings between women's groups and community members after seven months and at least once more during the intervention period. MIRA employees will be present at these meetings. After completion of the study, we will disseminate the results formally at meetings for all VDCs of Makwanpur district. We will invite VDC representatives, health management committee members, health post in-charges, teachers, user group members, NGOs, CBOs, local intellectuals, political party representatives, cooperative members, VDC secretaries, club members and local residents. After presenting the findings, the forum will be open for discussion and comment and feedback will be taken. Likewise, we will disseminate the findings at district level. The District Health Officer, District Public Health Officer, Local Development Officer, Community Development Officer, Regional Administrator, Women's Development Officer, Municipality Chief and representatives of International NGOs and NGOs working in the women's and children's sectors will be invited to the meeting. We will engage in open discussion at these meetings.

Nationally, we consulted the GoN Family Health Division prior to seeking ethical approval for the study, and continue to discuss the study with them. We have learned from GoN experience with health management committee strengthening, and have shared experience and tools to implement emergency obstetric first aid training in Makwanpur. We hope that by actively engaging the GoN in our research they will use our findings to inform the development of policy for maternal and newborn health. We will disseminate our findings to policy makers, programme managers and representatives of international organizations working in Nepal. We will also present our research at national conferences of professional bodies, for example the Perinatal Society of Nepal (PESON), Nepal Society of Obstetricians and Gynaecologists (NESOG), Nepal Pediatric Society (NEPAS) and the Nepal Medical Association (NMA), and at Tribhuvan University. We will publish relevant aspects of the study in national medical journals associated with these professional bodies. We will also summarise research findings on the MIRA website.

Internationally, we will publish articles in peer-reviewed journals, which have a history of influencing health policy. Through connections facilitated by a Wellcome Trust Strategic Partnership, we will disseminate the findings and recommendations to public health academics, policymakers, bilaterals and international NGOs. Our Strategic Partnership will build a communications strategy and seek resources to disseminate and engage the public in our research findings. We will engage stakeholders through policy briefs, conferences, workshops and websites.

## Abbreviations

ANM: Auxiliary Nurse Midwife; BEOC: Basic Emergency Obstetric Care; CBO: Community Based Organisation; CEOC: Comprehensive Essential Obstetric Care; CONSORT: Consolidated Standards of Reporting Trials; DAMOCLES: Data Monitoring Committees: Lessons, Ethics, Statistics; FCHV: Female Community Health Volunteer; GoN: Government of Nepal; HMC: Health Management Committee; HP: Health Post; IMCI: Integrated Management of Childhood Illness; MCHW: Maternal and Child Health Worker; MDG: Millennium Development Goals; MIRA: Mother Infant Research Activities; MMR: Maternal Mortality Ratio, maternal deaths per 100 000 live births; NEPAS: Nepal Paediatric Society; NESOG: Nepal Society of Obstetricians and Gynaecologists; NGO: Non Governmental Organisation; NMA: Nepal Medical Association; NRs: Nepali Rupees; PESON: Perinatal Society of Nepal; PHC: Primary Health Care Centre; RDBMS: Relational Database Management System; SBA: Skilled Birth Attendant; SHP: Sub Health Post; UCL: University College London; VDC: Village Development Committee; WHO: World Health Organisation.
